## Abstract

**Background:**

A complication of elective cesarean section (CS) delivery is its interference with the normal intestinal colonization of the infant, affecting the immune and metabolic signaling in early life— a process that has been associated with long-term morbidity, such as allergy and diabetes. We evaluate, in CS-delivered infants, whether the normal intestinal microbiome and its early life development can be restored by immediate postnatal transfer of maternal fecal microbiota (FMT) to the newborn, and how this procedure influences the maturation of the immune system.

**Methods:**

Sixty healthy mothers with planned elective CS are recruited and screened thoroughly for infections. A maternal fecal sample is taken prior to delivery and processed according to a transplantation protocol. After double blinded randomization, half of the newborns will receive a diluted aliquot of their own mother’s stool orally administered in breast milk during the first feeding while the other half will be similarly treated with a placebo. The infants are clinically followed, and fecal samples are gathered weekly until the age of 4 weeks, then at the ages of 8 weeks, 3, 6, 12 and 24 months. The parents fill in questionnaires until the age of 24 months. Blood samples are taken at the age of 2–3 days and 3, 6, 12 and 24 months to assess development of major immune cell populations and plasma proteins throughout the first years of life.

**Discussion:**

This is the first study to assess long-time effects on the intestinal microbiome and the development of immune system of a maternal fecal transplant given to term infants born by CS.

**Trial registration:**

ClinicalTrials.gov NCT04173208, registration date 21.11.2019.

**Supplementary Information:**

The online version contains supplementary material available at 10.1186/s12887-022-03609-3.

## Background

Microbes colonizing newborn infants at birth and during the first weeks of life are considered important, and perturbation to this process of colonization is associated with disruption of the stereotypic immune system development early in life [1, 2]. Early disturbances in gut microbiome have been associated with a multitude of inflammatory diseases, such as the development of autoimmune diseases [3], allergic diseases and atopy [4, 5], asthma, type I diabetes [6], and inflammatory bowel diseases [7, 8]. A recently published population cohort study also showed that compared with vaginally-delivered (VD) infants, the risk of infection-related hospitalization was greater among those born by cesarean section (CS) [9]. The difference of the early colonizing microbiome was thought to be one of the associating factors [9, 10].

The first stools of the newborns, the meconium, contain very low amounts of bacterial DNA and their composition differs greatly from that of later stool samples. The stool microbial communities develop along similar and time-dependent trajectories, in the absence of treatment with antibiotics [11, 12]. During the postnatal period the gut microbiome of VD and by CS-delivered infants differs markedly from each other [12–16] and this difference persists throughout the first years of life [17]. The disturbed transmission of the maternal gastrointestinal bacteria (particularly pioneering *Bacteroides* and *Bifidobacterium* species) through delivery by CS and maternal intrapartum antibiotic prophylaxis predispose newborn infants to colonization by potentially clinically important opportunistic pathogens that circulate in the hospital environment [16]. Infants born by CS have a less diverse intestinal microbiome and lower Th1 response than those born by vaginal delivery [18].

Various studies show that the intestinal microbiome influences vaccine responses, especially early in life [19–21]. Pneumococcal vaccine response can be studied for example by measuring serotype specific IgG antibodies. Finnish children are vaccinated with the pneumococcal conjugate vaccine at the age of 3, 5 and 12 months.

Due to the anticipated impact of disturbed microbial development on the developing immune system associated with delivery by CS, many researchers have tried to alleviate the effect of CS delivery on child microbiota. Treating the mother and breastfed child with a multispecies probiotic supplement may correct undesired changes in microbiota composition and function caused by cesarean birth [22]. Breastfeeding has a significant role in shaping the microbiota for example because of its oligosaccharides. Fucosylated oligosaccharides in mother's milk may also alleviate the effects of cesarean birth on infant gut microbiota [23]. A recent study reported that the microbial composition of breast milk was associated with the birth mode and exposure to intrapartum antibiotics [24].

Maternal probiotic supplementation has been shown to decrease the development of atopic dermatitis in the offspring [25]. In a 5-year and later on 13-year follow-up, probiotic intervention protected CS-delivered children from allergic disease and eczema [26, 27]. However, the topic is controversial and there is lack of evidence that probiotics prevent other chronic immune-mediated diseases.

Vaginal microbial transfer has been suggested to partially restore the intestinal microbiome of CS-delivered infants [28]. However, the vaginal microbiome is limited to mainly *Lactobacillus spp*. and does not contain the microbes that are abundant in the gut microbiota of the infant or the mother [14]. In addition, vaginal lactobacilli do not colonize the gastrointestinal tract of neonates but only pass it transiently, and their relevance for long-term health remains unclear [14, 29]. Hence, we recently reported that a fecal transfer from the infant’s own mother could restore rapidly and significantly the microbiome of CS-delivered infants towards that of those born vaginally [30]. Among the 17 mothers recruited, seven were selected after careful screening. Their infants received a diluted fecal sample from their own mothers, taken prior to delivery. Following a 3-month follow-up, all seven infants presented an uneventful clinical course without any adverse effects. The temporal development of the fecal microbiota composition of FMT-treated CS-delivered infants no longer resembled that of untreated CS-delivered infants but showed significant similarity to that of VD infants.

The implication of this study is that maternal fecal microbiota transplantation (FMT) mimics the natural transfer of microbiota from mother to VD infants.

Here, we present a protocol for randomized, double-blinded placebo-controlled clinical trial of orally delivered FMT from mothers to their CS-delivered infants, with a two-year follow-up period. The aim of the trial is to study the differences in microbiota between infants born by CS that received maternal fecal microbiota or a placebo transplantation, and to gain insight into the mechanisms involved in immune development and its association with early microbiota composition.

## Significance

### Study purpose

To the best of our knowledge, this is the first randomized study to assess whether maternal fecal transplant can be used as a method to close the gap in the heterogeneity of the intestinal microbiota of CS-delivered infants compared with the VD infants. In addition, it gives a unique possibility to study the interaction of gastrointestinal microbiome with the development of immunity during infancy.

## Study design

One hundred healthy pregnant women scheduled for elective CS at term, are recruited at 35–37 weeks of gestation during a visit for the assessment of mode of delivery (Fig. 1) at Women’s Hospital, Helsinki and Jorvi Hospital, Espoo, Finland. Maternal exclusion criteria are age below 18 years, gestational diabetes that requires medication, use of regular medication, known or suspected fetal congenital abnormality, travelling abroad within the last three months and antibiotic treatment within 3 months of delivery (excluding the prophylactic cefuroxime (or other in case of allergy) given prior to the elective CS). Non-elective CS is an exclusion criterion.

**Fig. 1 Fig1:**
[figure not shown]
Flowchart of SECFLOR Main Study

The midwifes and doctors inform potential mothers of the study at the visit and those who are interested to participate are contacted by the study nurse.

After informed consent, the pregnant woman is tested for potential contagious diseases as explained below (Table 1). Resulting from the screening process, a 40% exclusion rate is expected because of *group B streptococci* (GBS) carrier state (24% of pregnant women in our region) [31] and other positive findings in the screening samples.

**Table 1 Tab1:** Screening samples from the mother

**Blood tests**
Complete Blood Count, Erythrocyte sedimentation rate, C-reactive protein, Alanine transaminase, Alkaline phosphatase, Gamma-glutamyl transferase, Albumin, Creatinine, HIV, Hepatitis B, C and E, Treponema pallidum, Human T-cell leukemia virus
**Vaginal and perineal screening**
Group B *Streptococcus*, Methicillin-resistant *Staphylococcus aureus* (MRSA), Extended Spectrum Beta Lactamase (ESBL)
**Fecal screening**
* Salmonella, Shigella, Campylobacter, Yersinia enterocolitica/pseudotuberculosis,* Enterohemorragic *E. coli* (EHEC), Enteroaggregative *E. coli* (EAEC), Enteroinvasive *E. coli* (EIEC), Enterotoxigenic *E. coli* (ETEC), Enteropatogenic *E. coli* (EPEC), *Clostridium difficile*, Parasites, Noro virus, Multi drug resistant gram negative bacteria (MDRGN), Vancomycin Resistant *Enterococcus* (VRE), *Listeria monocytogenes, Helicobacter pylori*, Sars-CoV-2

The eligible women are randomized into placebo (*GP*, 30 women), and intervention group *(GI*, 30 women). The randomization 1:1 is done in blocks of 4 mothers. The study is double blinded. The laboratory technicians who prepare the FMT product also perform the computer-generated randomization.

For promoting the study, we have set up posters and informed the staff at the maternity clinics, and used social media.

A fecal sample of 100 g and a blood sample of 15 mL are collected from the mother approximately two weeks prior to scheduled CS for screening of contagious diseases (Fig. 1). The mother divides the feces into the administered sample tubes according to written instructions. Feces for the transplant is collected into an empty tube using a spoon in the cap. The mother informs the research nurse, who delivers the tubes taken for screening to the laboratory as soon as possible, where the transplant is prepared from the fresh sample – this process is completed with a 6 h time frame.

The fresh fecal sample is screened for the presence of parasites and pathogenic viruses and bacteria (Fig. 1, Table 1). An aliquot (0.125 g) of the fresh fecal sample is used to determine the bacterial composition of the sample. Another part of this fresh sample is used as the transplant and for that purpose 1 g of feces is dissolved in 15 mL of isotonic saline and 10% glycerol, homogenized, and the 0.5 mL aliquots of the transplant are immediately frozen and stored at -80 °C [32].

At delivery, the transplant is thawed and 0.5 mL representing 3.5 mg of the mother’s fecal sample is dissolved in 5 mL of the mother’s own milk or when not available pasteurized bank milk. The sample is given orally to newborn infants born to *GI (Intervention group)* mothers within 2 h of delivery. The newborn infants born to *GP* (*Placebo group)* mothers are given 0.5 mL of isotonic saline dissolved in 5 mL of pasteurized bank milk or mother’s own milk as described earlier. The randomization is performed on the day of the scheduled CS and 0.5 mL of either transplant or placebo is delivered to the ward on ice in a black polypropylene tube for blinding purposes.

Infant exclusion criteria are Apgar score of less than 8 at 5 min of age, birth weight below 2500 g or above 4500 g, disturbances of neonatal adaptation (such as transient tachypnea of the newborn) and antibiotic treatment of the newborn before discharge. In case of a suspected infection of the newborn the randomization code can be opened.

After the first feeding the newborn is observed for potential reactions, such as increased peristalsis, diarrhea, vomiting, fever, and rash. Possible adverse events are reported to the electronic database. Before discharge, typically on postnatal day 2, a 3 mL blood sample is gathered from the newborn for the assessment of white cell count, C-Reactive Protein (CRP) and hemoglobin, and for detailed immunological analyses. The sample is taken at the routine sampling for metabolic screening.

During the hospital stay two fecal samples are collected from the newborn: on the day of birth and third day of life (Fig. 1).

From the first postnatal week on, the infant is followed in the well-baby clinic according to national protocols. As a part of the study, the parents can be in contact with the study nurse and pediatrician by telephone. Fecal samples of the infant are taken weekly for the first 4 weeks, and at 8 weeks and 3 months, by the parents. Fecal sample from the mother is taken 4 weeks postpartum. Samples are temporarily stored at − 20 °C in the home freezer before transfer in frozen form to − 80 °C. (Fig. 1).

Breastfeeding mothers give a breast milk sample at 2 and 8 weeks postpartum. Milk samples are temporarily stored at − 20 °C in the home freezer before transfer in frozen form to − 80 °C.

At 3 months postnatally, the study nurse visits the family homes. The visit is timed before the second orally given rota virus vaccination, if possible. Data from growth measurements performed at the well-baby clinic visits are gathered. Fecal samples of the infant and the mother (4 weeks post partum) stored in the home freezer are collected during the visit. A capillary blood sample of 1–1.5 mL is collected by the study nurse. The families have the possibility to meet with the study pediatrician (Fig. 1).

At 6 months of age fecal samples are collected from the mother and infant and a 3 mL blood sample is collected from the infant at a laboratory.

At 12 months of age, a follow-up visit to the study nurse takes place for all families for the assessment of growth (Fig. 1). Also, data from growth measurements performed at the well-baby clinic visits are gathered as well as vaccination status. A week prior to the visit, fecal samples of the infant and the mother are taken by the parents and stored at -20 °C in the home freezer and delivered at the visit. At the visit a 5 mL blood sample is collected. The families have the possibility to meet with a pediatrician. The families are also given a sealed envelope containing information of the allocation group.

At 24 months of age, a follow-up visit to the study nurse takes place (Fig. 1). The visit, including collecting fecal samples from mother and child, and a 5 mL blood sample from the child, is identical to the follow-up visit at the age of 12 months.

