## Outcome

### Microbiome

The primary outcome of the study is the difference in composition of the intestinal microbiome, specifically diversity and relative abundances of Bacteroides spp., Bifidobacterium spp. as well as known pathobionts between the two groups at 3 months of age. We use beta-diversity between the microbiota profiles of the two groups calculated by PERMANOVA as described previously [46]. The analysis of the gut microbiome is performed at 12 months (including previous sequential samples) and at 24 months. Unblinding for the parents is done at 12 months and for the research group at 24 months.

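### Two recruiting hospitals, but hospital appears in neither the stated allocation rule nor the stated primary comparison: no bias, but avoidable chance imbalance and some lost precision

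*Protocol article*

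**What the plan says.** All references are to the protocol article.

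- **Sites.** Under Study design, mothers are recruited "at Women’s Hospital, Helsinki and Jorvi Hospital, Espoo, Finland". The split between the two hospitals is not given.
- **Allocation.** The text after Table 1 says "The eligible women are randomized into placebo (*GP*, 30 women), and intervention group *(GI*, 30 women") and "The randomization 1:1 is done in blocks of 4 mothers". It also says who randomises (the laboratory technicians who prepare the product), and later that this happens on the day of the section. No stratification factor is named.
- **Primary outcome.** Under Outcome, Microbiome, it is the difference in composition, "specifically diversity and relative abundances of Bacteroides spp., Bifidobacterium spp. as well as known pathobionts between the two groups at 3 months of age". The test is a PERMANOVA on beta-diversity between the two groups, with a reference for the method. No hospital term is mentioned.
- **Background.** Section delivery and intrapartum antibiotics are said to predispose infants to colonisation by "potentially clinically important opportunistic pathogens that circulate in the hospital environment".

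**The concern.** Blocks that run across both hospitals balance the arm totals but not the arms within each hospital. The Background gives a reason to think that the place of birth could matter for the organisms measured, and pathobionts are a named part of the primary outcome. If the two hospitals differ in what infants carry at 3 months, two things follow from leaving hospital out of both allocation and test:

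- one hospital can be over-represented in one arm by chance, which complicates the reading of that one allocation;
- variation between hospitals stays in the residual distances and reduces sensitivity, whether or not the arms are imbalanced.

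With 30 infants per arm, there is little room for either.

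**Working it through.** **Inputs from the article.** 100 mothers recruited, 40% lost at screening, 1:1 allocation, blocks of 4, two hospitals.

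**Inputs assumed, because the article does not give them.** Share of the larger hospital p = 0.5, 0.65 or 0.8. Hospital effect g = 0, 0.5 or 1 SD on a single index, compared by a two-group t-test as a stand-in for PERMANOVA.

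**1. The article's own figure.** 100 × (1 − 0.40) = 60. 60 / 4 = 15 complete blocks, so exactly 30 per arm. This reproduces.

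**2. Imbalance with one list across hospitals.** If hospital is unrelated to position in the list, the two arm counts are independent Binomial(30, p). The SD of the difference in hospital share is √(2p(1−p)/30). A 20-point difference is 6 of 30 infants. The probabilities are exact binomial; simulation of the blocked lists agrees to within about 0.3 percentage points.

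| Hospital split | SD of difference | P(≥10 points) | P(≥20 points) | P(≥30 points) |
|---|---|---|---|---|
| 50:50 | √(0.50/30) = 0.129 | 51.9% | 15.5% | 2.7% |
| 65:35 | √(0.455/30) = 0.123 | 49.9% | 13.6% | 2.1% |
| 80:20 | √(0.32/30) = 0.103 | 41.8% | 7.5% | 0.6% |

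**3. Imbalance with blocks of 4 within each hospital.** Only the last block in each hospital can be incomplete, so the arms differ by at most 2 infants per hospital, or about 2/30 = 6.7 points. In simulation the SD was 2.2 to 2.5 points, the largest difference was 6.7 points, and none reached 10.

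**4. Effect on the unadjusted test, 60 infants, 65:35 split, one list (simulated).**

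| Hospital effect | Mean bias | SE | Type I error |
|---|---|---|---|
| 0 | 0.00 | 0.258 | 4.9% |
| 0.5 SD | 0.00 | 0.264 | 4.8% |
| 1 SD | 0.00 | 0.285 | 4.9% |

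The SE rises by 0.2641/0.2579 − 1 = 2.4% and 0.2854/0.2579 − 1 = 10.7%. The formula √(1 + g²p(1−p)) gives 2.8% and 10.8%. Across the three splits it gives 2.0% to 3.1% at 0.5 SD and 7.7% to 11.8% at 1 SD.

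**5. The same test, given that an imbalance of 20 points or more has occurred.**

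- Hospital effect 0.5 SD: the estimate shifts by 0.11 to 0.12 SD, and the false-positive rate in those trials is about 7%.
- Hospital effect 1 SD: the shift is 0.23 to 0.24 SD, and the rate is about 11%.

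These are offset by rates below 5% in the remaining trials, so the overall rate stays at 5%.

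**The case against.** Four arguments carry weight.

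- **The article is condensed.** It does not say that a single list serves both hospitals, or that the model excludes hospital. The full protocol or analysis plan may stratify or adjust. This stands. The point concerns the rule and the test as stated, and one confirming sentence would settle the allocation half.
- **Randomisation already deals with chance imbalance.** A reader might infer that hospital confounds the primary outcome. The documents do not support that: assignment does not depend on hospital, expected bias is zero, and the type I error is nominal (step 4). The rates in step 5 describe an unlucky subset of trials, not the design.
- **The Background does not say that these two hospitals differ.** A reader might infer that the protocol itself identifies the site as a source of the organisms compared. The sentence concerns hospital flora in general, as an explanation of how section delivery alters colonisation, and every infant in the trial is exposed to some hospital environment. A difference between the two hospitals is an assumption here. Discharge is typically on day 2 and the outcome is at 3 months, so such a difference would also have to persist.
- **The size is modest.** On the assumed splits, about 85% to 93% of trials never reach a 20-point imbalance. At 20 points with a 0.5 SD hospital effect, the shift is 0.2 × 0.5 = 0.10 SD, about 0.4 of one SE.

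These arguments remove any claim of bias or error. They do not remove the case for a nearly costless precaution in a two-hospital trial of 60.

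**Conclusion.** The point holds as a recommendation on design and analysis. Nothing in the article is contradictory or invalid here. As stated, the allocation rule and the primary comparison leave out hospital. The consequence is a chance of roughly 7% to 15% that the hospital share differs between arms by 20 points or more and, if the hospitals differ, an SE about 2% (0.5 SD) to 11% (1 SD) larger at a 65:35 split. There is no systematic bias and no inflation of type I error.

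The conclusion rests on three assumptions: the hospital split, the existence and size of a hospital effect lasting to 3 months, and a t-test on one index in place of PERMANOVA. If the hospitals do not differ, nothing is lost under the present plan, and the change costs almost nothing.

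**What to change.** - **If allocation can still be changed:** use a separate list in blocks of 4 for each hospital, include hospital as a term in the primary PERMANOVA, and restrict its permutations within hospital.
- **If allocation has already run on one list:** make the hospital-adjusted analysis with within-hospital permutations the primary one. Record this before the research group is unblinded, which the article places at 24 months.
- **If the full protocol already stratifies by hospital:** say so, and carry the stratum into the primary test.

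The cost is a second computer-generated list, at most one incomplete block per hospital (so the arms may not end at exactly 30:30), one degree of freedom and one model term. No new data and no change to clinical care are needed.

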## Methods

### Fecal samples

The maternal transplant is prepared from a fresh fecal sample taken at least one week before elective CS and within 6 h of donation prepared as described [32], and frozen at -80C.

For the follow-up samples, a home sampling kit is provided for fecal samples of the mother and of the infant’s feces from diapers. The intestinal microbiota of mothers and infants is determined using 16S rRNA gene amplicon sequencing using the MiSeq sequencing [22, 23]. Fecal DNA is extracted by repeated bead beating from ca. 125 mg of fecal material [33] and processed for sequencing of the hypervariable V3-V4 region of the 16S rRNA gene using primers 341F 5′-CCTACGGGNGGCWGCAG-3′ and 785R 5’-GACTACHVGGGTATCTAATCC-3′ [15, 34] and barcoding primers from Kozich et al. [35] as explained in detail elsewhere [36]. The pooled libraries are sequenced with Illumina MiSeq platform using a MiSeq v3 reagent kit (MS-102–3003) with 5% PhiX as spike-in (Illumina).

The DNA sequences are processed and analyzed using the R-package mare [37, 38], which uses USEARCH and ASVs for read processing, and taxonomic annotation [39]. DNA extractions and MiSeq runs are processed in a time frame of 12 months and include internal reference samples and, if requested, a mock community [40, 41]. Metagenomic analysis is conducted essentially as previously demonstrated [42]. In brief, Nextera XT libraries are sequenced with Illumina Novaseq with the target of 7 Gbp of sequence per sample at the sequencing laboratory of the Institute for Molecular Medicine Finland FIMM Technology Centre, University of Helsinki. Filtered reads are assembled with Metaspades and Megahit and ORFs are predicted with Prodigal. Species level community profiling based on marker genes are done using Metaxa2. Resistance genes are characterized by mapping metagenomic reads with Bowtie2 against the CARD and Resfinder databases to search for acquired antibiotic resistance genes [42].

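### The printed recipe puts about 28 to 33 mg of feces in each 0.5 mL dose, but the protocol states 3.5 mg

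*Protocol article*

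**What the plan says.** Both statements are in the Study design section of the protocol article.

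- **Preparation** (text following Table 1): "1 g of feces is dissolved in 15 mL of isotonic saline and 10% glycerol, homogenized", after which "the 0.5 mL aliquots of the transplant are immediately frozen and stored at -80 °C".
- **Administration** (the paragraph beginning with delivery): "the transplant is thawed and 0.5 mL representing 3.5 mg of the" mother's fecal sample. This is mixed into 5 mL of milk and fed to the newborn within 2 hours of birth. The same paragraph says that "0.5 mL of either transplant or placebo is delivered to the ward on ice".

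Two other places bear on the dose without giving a concentration. The Methods paragraph of the Abstract says that "half of the newborns will receive a diluted aliquot of their own" mother's stool. The Fecal samples section says the transplant is "within 6 h of donation prepared as described [32], and frozen at" −80 °C, so it refers the preparation to a cited method.

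**The concern.** The volume is 0.5 mL at every step: frozen, thawed and sent to the ward. With a fixed volume, the concentration of the suspension determines the mass of feces given. The recipe fixes that concentration, and it does not agree with the stated mass.

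The mass of maternal feces is the investigational exposure, given by mouth to newborns. From this document a reader cannot tell whether it is about 3.5 mg or about 30 mg. A group that followed the printed recipe and gave 0.5 mL would deliver 8 to 9.5 times the printed mass. If the wrong figure reaches the trial report, the safety observations and microbiome effects will be attached to the wrong dose.

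**Working it through.** **Inputs, all from the Study design section**

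- Feces in the preparation: 1 g = 1000 mg
- Diluent: 15 mL of isotonic saline and 10% glycerol
- Portion frozen, thawed and delivered: 0.5 mL
- Stated mass in that portion: 3.5 mg

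**Formula:** mass per dose (mg) = 1000 mg / total volume (mL) × 0.5 mL.

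The text does not say whether 15 mL is the final volume, whether glycerol is added on top, or how much volume the feces take up. I assumed 0 to 1 mL for 1 g of feces and tried each reading.

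| Reading of the total volume | Total (mL) | Mass in 0.5 mL (mg) | Ratio to 3.5 mg |
|---|---|---|---|
| 15 mL is the total | 15 | 33.3 | 9.5 |
| 15 mL + 1 mL feces | 16 | 31.25 | 8.9 |
| 15 mL saline + 1.5 mL glycerol | 16.5 | 30.3 | 8.7 |
| 15 mL saline made up to 10% glycerol (15/0.9) | 16.67 | 30.0 | 8.6 |
| 16.5 mL + 1 mL feces | 17.5 | 28.6 | 8.2 |
| 16.67 mL + 1 mL feces | 17.67 | 28.3 | 8.1 |

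No reading reproduces the stated 3.5 mg.

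**What 3.5 mg would require.** A mass of 3.5 mg in 0.5 mL is 7 mg/mL. That needs one of the following:

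- 1 g made up to 1000 / 7 ≈ 143 mL
- only 7 × 15 = 105 mg of feces in 15 mL
- a dose of 3.5 / (1000/15) ≈ 0.05 mL of the printed suspension

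None of these is described.

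**Possible reconciliations**

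- *Milk.* Adding 0.5 mL to 5 mL changes the volume, not the mass. The 3.5 mg is in any case attached to the 0.5 mL before mixing.
- *Only 0.5 mL of the 5.5 mL milk mixture is fed.* 33.3 × 0.5/5.5 = 3.0 mg, down to 28.3 × 0.5/5.5 = 2.6 mg. Neither equals 3.5 mg, and the text mentions no partial feed.
- *An unprinted 1:10 dilution.* 33.3/10 = 3.3 mg, down to 28.3/10 = 2.8 mg. These are near 3.5 mg but not equal to it.
- *Dry rather than wet mass.* This would need a dry fraction of 3.5/33.3 = 10.5% to 3.5/28.3 = 12.4%. The text attaches the mass to the mother's fecal sample and never mentions dry weight.

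**The case against.** The best defence is that the article condenses a fuller protocol and leaves the preparation to a cited method that is not at hand. A laboratory dilution step is the kind of detail an article may leave out, and the Abstract does call the product diluted. One tenfold step at the 15 mL reading gives 3.33 mg, within about 5% of the stated figure (3.33/3.5 = 0.95). On that account 3.5 mg is roughly right and one line is missing from the recipe. The defence adds that the dosed volume is consistent throughout, that no misdosing is shown, and that arms, allocation, outcome, sample size and error rates are the same at either mass.

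Much of this stands. An omitted dilution is plausible, the document does not show that 3.5 mg is the wrong figure, and no inference is affected. The defence does not remove the contradiction, however. The article chose to print both a recipe and the resulting mass, and as printed they cannot both be true. A further step in the cited method would show that the recipe is incomplete, which is itself the defect. The recipe also goes from homogenizing to immediate freezing of 0.5 mL portions, and the administration text goes from thawing to 0.5 mL, so neither leaves an evident place for a dilution. The Abstract's word may refer only to the saline suspension or to the milk, and it comes with no factor.

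**Conclusion.** The concern holds. By the printed recipe a 0.5 mL dose contains 28.3 to 33.3 mg of feces, against 3.5 mg stated, a factor of 8.1 to 9.5. The upper figure uses only printed numbers. The lower one also assumes that glycerol is added on top of 15 mL and that 1 g of feces takes up 1 mL, and even then the gap is about eightfold.

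Either the recipe omits a roughly tenfold dilution or the stated mass is wrong, and the document does not settle which. The defect lies in the description of the intervention. It is not evidence of a dosing error or of variation between infants, and it does not touch the randomized comparison or the power statement. It should be corrected because it concerns the exposure given to newborns.

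**What to change.** Check the laboratory's preparation procedure and records, then correct the statement that does not describe practice:

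- If a dilution step exists, add it and its factor to the recipe in the Study design section, and confirm that the result agrees with the stated mass.
- If there is none, restate the mass in the administration paragraph as about 33 mg, or as the value for the confirmed final volume.

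Report the confirmed dose with the trial results. Recording the mass infant by infant is needed only if the check shows that preparations differed.

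The cost is one check of the procedure and records and a one-line correction. Sample size, visits and dosing do not change.
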